## Abstract

**Introduction:** Acute stroke care delivered by interdisciplinary teams is time-sensitive. Simulation-based team training is a promising tool to improve team performance in medical operations. It has the potential to improve process times, team communication, patient safety, and staff satisfaction. We aim to assess whether a multi-level approach consisting of a stringent workflow revision based on peer-to-peer review and 2–3 one-day *in situ* simulation trainings can improve acute stroke care processing times in high volume neurocenters within a 6 months period.

**Methods and Analysis:** The trial is being carried out in a pre-test-post-test design at 7 tertiary care university hospital neurocenters in Germany. The intervention is directed at the interdisciplinary multiprofessional stroke teams. Before and after the intervention, process times of all direct-to-center stroke patients receiving IV thrombolysis (IVT) and/or endovascular therapy (EVT) will be recorded. The primary outcome measure will be the “door-to-needle” time of all consecutive stroke patients directly admitted to the neurocenters who receive IVT. Secondary outcome measures will be intervention-related process times of the fraction of patients undergoing EVT and effects on team communication, perceived patient safety, and staff satisfaction via a staff questionnaire.

**Interventions:** We are applying a multi-level intervention in cooperation with three “STREAM multipliers” from each center. First step is a central meeting of the multipliers at the sponsor's institution with the purposes of algorithm review in a peer-to-peer process that is recorded in a protocol and an introduction to the principles of simulation training and debriefing as well as crew resource management and team communication. Thereafter, the multipliers cooperate with the stroke team trainers from the sponsor's institution to plan and execute 2–3 one-day simulation courses *in situ* in the emergency department and CT room of the trial centers whereupon they receive teaching materials to perpetuate the trainings.

**Clinical Trial Registration:** STREAM is a registered trial at https://clinicaltrials.gov/ct2/show/NCT03228251.

## Introduction

The benefits of acute stroke therapy critically depend on the time to recanalization of the occluded brain vessel. This has been consistently shown for intravenous thrombolysis (IVT) (1) and endovascular thrombectomy (EVT) (2), nowadays applied to 5–25 or 5–10% of all patients suffering from an ischemic stroke, respectively. Each minute lost reduces therapeutic efficacy and increases the risk of complications (3, 4). When implementing these therapies into daily clinical practice, stroke teams have to strive for optimal process times in order to translate the benefits shown in clinical trials into good outcomes for the patients. Since the widespread introduction of EVT, the chain of acute stroke treatment has become more complex. The patient is cared for by an interdisciplinary team (5) and has to undergo several handovers with possible interface problems.

As treatment delays, errors or misjudgements may put the patient at risk, the initial assessment, diagnostic procedures and therapeutic decisions have to be as fast as possible without losing accuracy. The decision to start IVT and/or EVT should be completed within <30 min, which requires a well-functioning workflow including initial assessment, blood sampling, the organization of further processes, transport, and radiological diagnostics. Recent reports show that excellent process times can be reached at high volume centers but not as reliably at the majority of smaller stroke units worldwide (6, 7). So far, reports on workflow improvement in the setting of acute stroke care have focussed on streamlining of the process but how the teams that work along these processes are actually trained has not been detailed (8, 9). It is a well-recognized phenomenon that time pressure increases the risk of medical errors and puts strain on team communication. Complications and adverse events during medical treatment are a frequent problem (10). In 2010, up to every fourth patient treated in a hospital may have suffered from avoidable medical complications (11, 12). Medical complications caused by human failure are estimated to represent 3–4% of the health expenditure. Approximately 70% of these cases are attributed to human factors, such as miscommunication, forgotten or falsely executed orders, mix-ups, or wrong decisions (13).

One means to counteract the deleterious effect of time pressure on team communication is crew or crisis resource management (CRM), which is a work and training philosophy combining different strategies for teams focusing on non-technical skills in high-reliability environments where human error can have a devastating effect (14). CRM concepts, which were originally designed for aviation, have been modified and adapted to a wide range of high-reliability environments where people have to make time-critical wide-ranging decisions, such as in emergency medicine. Previously, the trial sponsor (University Hospital Frankfurt, Germany) designed a stroke team training for the interdisciplinary multiprofessional team of its neurocenter using an *in situ* simulation along the entire chain of acute stroke care from the paramedics' handover to the beginning of the neurovascular intervention. We introduced the principles of CRM into our stroke care protocol with a focus on communication skills, a defined team, a binding algorithm involving the specific division of tasks and predefined “check points” for a brief team time-out (15). In order to acquaint the staff with the algorithm, we implemented monthly simulation training with a high-fidelity manikin. This intervention was highly efficient (16). We transferred a trimmed-down version of the intervention—relying on a peer-to-peer review of the respective acute stroke algorithms and a one-time simulation training—to our regional stroke network consisting of stroke units of different certification levels where it significantly reduced the network-wide median door-to-needle time in a pre-test-post-test analysis (17).

The STREAM trial is directed at high level stroke centers with 24/7 EVT capacity in a controlled prospective pre-test-post-test design. It will assess the immediate effect of a composite intervention that includes a peer-to-peer review of each center's acute stroke algorithm, which defines the team's composition and details the specific tasks of each team member. This is in combination with a short course of repetitive stroke team simulation training. We hypothesize that the implementation of a stroke team algorithm (defined team with precisely defined tasks), applying the principles of crew resource management (CRM) and stroke team simulation training with a focus on efficient teamwork and communication will improve the processing time, patient safety, and staff satisfaction.

## Methods and Analysis

### Design

STREAM is a prospective single-arm multicenter trial with a pre-test-post-test design (Figure 1) and central data monitoring, employing individual patients' case report forms (Supplemental Data 1) to record the baseline variables, processing time, time-consuming items in the acute stroke workflow, and the team's composition. Additionally, staff questionnaires will be used to capture satisfaction regarding interdisciplinary teamwork, safety climate, stress recognition and error handling as well as general job satisfaction and identification within the workplace.

**Figure 1 F1:**
[figure not shown]
Timeline of the STREAM trial.

### Interventional Methods

During a 3-months pre-test period, the participating seven stroke centers (tertiary care university hospitals with 24/7 thrombectomy, well-comparable to other tertiary stroke care centers) will record the data of all consecutive stroke patients directly admitted to the emergency departments. The participating centers are University Hospital Augsburg, University Hospital Tübingen, University Hospital Heidelberg, Ludwig Maximilians-University Munich, Center for Stroke Research Berlin Charité, University Medical Center Hamburg Eppendorf, University Hospital Cologne. University Hospital Frankfurt (Goethe University) is the sponsor of the trial and is not participating in the trial. All consecutive patients undergoing acute recanalization therapy (IVT and/or EVT) will be enrolled. Pre-test staff satisfaction and patient safety will be measured using a 67-item questionnaire, based on the Safety Attitudes Questionnaire (SAQ), a validated instrument used to measure the patient safety climate in clinical areas (18, 19). After the pre-test period (observation phase 1), the data acquisition will be paused for 6 months during which the intervention will take place.

We will perform a multi-level intervention in close cooperation with three “STREAM multipliers” per center. We recommended the centers to nominate one stroke neurologist, one neurointerventionalist and one nurse of the emergency department but left the final decision about the composition of the multiplier team to each center. The first step of the intervention will be a central meeting at the sponsor's institution (to accommodate shift plans etc., we will conduct two meetings with identical programmes and final written distribution of all protocols). The purpose of this first meeting will be a critical revision of each center's acute stroke algorithm in a peer-to-peer process that is captured in a protocol and provided to each center as well as a familiarization of the multiplier team with stroke simulation. To this end, there will be a demonstration of stroke team simulation and a seminar on basic principles of simulation training and debriefing as well as CRM and team communication. The protocol on each center's algorithm will encourage the implementation of an interdisciplinary stroke team with a binding and precise definition and assignment of tasks. Thereafter, the multipliers will cooperate with the sponsor's stroke team trainers to organize 2–3 simulation-based team trainings with a high-fidelity manikin *in situ* in each center's emergency department and CT room. Two of the training sessions shall be conducted by the stroke team trainers from the sponsor while the third training session will be encouraged to be led by one of the multipliers. This is with the aim of establishing the concept of stroke team training and simulation on a regular basis. The centers will be provided teaching materials for use at their institution and their regional stroke networks. The intervention shall be completed within 6 months.

During the following 3-month post-test period (observation phase 2), the participating seven centers will record the process times of all consecutive direct-to-center patients receiving recanalization therapy (IVT and/or EVT). Post-interventional staff satisfaction and perceived patient safety will be measured with a 67-item questionnaire.

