### Selection of Centers and Subjects

Centers were selected after a site selection screening taking into account the number of recanalization therapies per year, median process times and the readiness to participate with dedication in the intervention. Randomization into an instant and a delayed intervention cohort would be desirable. However, due to the limited number of stroke centers (*n* = 7) and their heterogeneity, this approach is not feasible. Therefore, all seven centers will undergo the intervention and observation phases simultaneously and a comparison will be made between the pre-test-post-test results of all seven centers grouped together.

All patients over the age of 18 years who are admitted directly to the participating centers and receive IVT (primary endpoint: door-to-needle time) in the context of an acute stroke are eligible irrespective of whether they receive additional EVT or not. If EVT is performed, then the EVT-specific processing time will also be acquired (secondary endpoints). Written informed consent will be obtained from all patients or their legal representatives before the transfer of data to the sponsor. Patients who had been secondarily transferred to the stroke centers for EVT (“drip-and-ship”) and patients suffering in-hospital stroke will be excluded from the trial.

Observation phase 1: All direct-to-center stroke patients receiving thrombolysis and/or thrombectomy in the 3 months before the intervention phase.

Observation phase 2: All direct-to-center stroke patients receiving thrombolysis and/or thrombectomy in the 3 months after the intervention phase.

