A pilot trial on the efficacy of a fixed stroke team algorithm and regular simulation-based stroke team training in our regional stroke network consisting of 7 stroke units showed a shortening of the network-wide median “door-to-needle” time by 12 min (43, IQR 30–60 to 31, IQR 24–42 min). A priori sample size calculation based on this data yielded a minimal number of 110 patients in each group to prove the comparative efficacy of the composite intervention on the primary endpoint with a statistical power of 0.8 and a type 1 error probability of <0.05. The seven tertiary care stroke centers perform 80–250 thrombolyses per year and should jointly be able to recruit 200 patients in each intervention phase considering the potential dropout rate for missing reports or informed consent in 1/3 of the patients. The centers will be explicitly motivated to record all consecutive patients and they will be obliged to prove that adequate efforts have been made via a monitored screening log.

We will present the median and 25–75 percent interquartile ranges (IQR) of the process times and test differences between the intervention phases for statistical significance via the Wilcoxon-Mann-Whitney Test. The answers provided within the questionnaire capturing satisfaction with the interdisciplinary teamwork, safety climate, stress recognition and error handling, as well as staff satisfaction and identification with the workplace, will be recorded using an ordinal 5-point Likert scale.

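### Door-to-needle time is compared only among patients given IVT, so a faster process cannot be told apart from a changed mix of treated patients, and no listed endpoint would show which occurred

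*Protocol article*

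**What the plan says.** **Who is analysed.** Under Selection of Centers and Subjects, adults admitted directly who "receive IVT (primary endpoint: door-to-needle time) in the context of an acute stroke are eligible". Data Analysis defines the primary endpoint as the median time from arrival to the alteplase bolus and compares the two phases with a Wilcoxon-Mann-Whitney test. No adjustment is stated, and all seven centers are grouped together.

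**What the intervention touches.** Interventional Methods describes a peer-to-peer revision of each center's acute stroke algorithm, followed by simulation training of the team that works to it. The Introduction sets the standard for that team: "therapeutic decisions have to be as fast as possible without losing accuracy".

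**What is recorded in each phase.** For the pre-test period, Interventional Methods says that the centers "will record the data of all consecutive stroke patients directly admitted to the emergency departments". The same paragraph then says "All consecutive patients undergoing acute recanalization therapy (IVT and/or EVT) will be enrolled". For the post-test period the centers "will record the process times of all consecutive direct-to-center patients receiving recanalization therapy (IVT and/or EVT"). Selection of Centers and Subjects defines the phases in matching words: "Observation phase 1: All direct-to-center stroke patients receiving thrombolysis and/or thrombectomy in the 3 months before the intervention phase" and "Observation phase 2: All direct-to-center stroke patients receiving thrombolysis and/or thrombectomy in the 3 months after the intervention phase". The Abstract likewise describes recording before and after for treated patients.

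**What else is measured.** Data Analysis lists EVT process times, haemorrhagic transformation, team composition, time-consuming processes and questionnaire items. The Discussion adds intra- and extracranial bleeding. Completeness is supported by a log: the centers are told that "they will be obliged to prove that adequate efforts have been made via a monitored screening log".

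**The concern.** A door-to-needle time exists only if the team decides to thrombolyse. In this design the post-test decision is made by a team whose algorithm and training have just been changed. If that team treats fewer slow, complicated cases, or more quick ones, the median falls although no step has become faster. If it treats more complicated cases, a real gain in speed is hidden. The rank test sees only two sets of times and responds to both causes alike.

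Two proportions would help a reader judge this: the share of suspected-stroke admissions given IVT, and the share of those treated whose final diagnosis is not stroke. Neither is a listed endpoint. The wording on eligibility does not settle whether a treated patient later found not to have a stroke belongs to the trial. If such patients are out, they are not seen. If they are in, no listed measure identifies them. On either reading, the accuracy half of the stated aim is not reported at patient level.

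The stakes are higher because the Discussion says that the centers were chosen with medians of 30 min or below and that improvement will be hard to show. A shift of one to three minutes could then matter to the conclusion.

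**Working it through.** **1. Reading the recording rules side by side.**
- Pre-test, broad sentence (Interventional Methods): all directly admitted stroke patients.
- Pre-test, enrolment sentence in the same paragraph: treated patients only.
- Post-test sentence (Interventional Methods): treated patients only.
- Formal definitions of both phases (Selection of Centers and Subjects): treated patients only, in matching words.
- Abstract, before and after: treated patients only.

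One sentence is broader than the others. The phases are formally alike, and nowhere does the article clearly commit to counting untreated patients in both.

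**2. Inputs for the size.** The article gives no figure for a selection effect, so there is none to reproduce. From Data Analysis: pilot medians 43 and 31 min (difference 12), post-period IQR 24–42, a minimum of 110 patients per group and 200 expected per phase. From the Discussion: baseline medians of 30 min or below. Assumed: log-normal times with the spread of the pilot post-period.

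Log SD = ln(42/24) / 1.349 = 0.5596 / 1.349 = 0.415.

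**3. Effect on the median with no change in speed.** If a fraction f of cases, all from the slow end, is no longer treated, the new median is the old quantile (1 − f)/2.
- f = 10%: 45th percentile, z = −0.1257. 31 × exp(−0.1257 × 0.415) = 29.4 min, a fall of 1.6 min.
- f = 20%: 40th percentile, z = −0.2533. 31 × exp(−0.2533 × 0.415) = 27.9 min, a fall of 3.1 min.

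Adding 10% extra cases, all faster than the new median, also leads to the old 45th percentile. These are ceilings: no other loss of the same share lowers the median further.

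**4. Effect on the planned test.** Two-sided Wilcoxon-Mann-Whitney at 0.05, 2,000 simulated trials per setting, with no true change in speed.

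Slowest cases no longer treated, baseline median 30 min:

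| Share lost | New median (min) | Rejection, n = 200 per phase | Rejection, n = 110 per phase |
|---|---|---|---|
| 0% | 30.0 | about 6% | 6% |
| 5% | 29.2 | 14% | 10% |
| 10% | 28.5 | 42% | 26% |
| 20% | 27.1 | 92% | 73% |

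A softer version, in which a slower case type becomes less common (simple cases with median 28 min):

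| Time ratio, complex to simple | Complex share, before to after | Median (min) | Rejection, n = 200 | Rejection, n = 110 |
|---|---|---|---|---|
| 1.5 | 30% to 20% | 31.5 to 30.2 | 15% | about 10% |
| 2 | 30% to 10% | 33.6 to 29.5 | 75% | 49% |

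With an unchanged share, rejection stayed between 4% and 6%. Read in reverse, the first softer scenario (20% to 30%) raises the median by 31.5 − 30.2 = 1.3 min and would mask a real gain of that size.

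**The case against.** **The mechanism is inferred.** The intervention is described as team composition, task assignment, communication and simulation. No change to IVT criteria is mentioned, and crew resource management is presented as a remedy for time pressure. This stands: the article does not show that selection will change. What remains is that the algorithm is revised before phase 2, that the speed of the treatment decision is itself a target, and that the planned comparison would not reveal a change if one occurred.

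**The needed data may already exist.** The CRF and the content of the screening log are not shown, and a condensed article may leave such details to the full protocol or the analysis plan. This also stands, so the point does not claim that a field or a count is missing. It rests on what the article does state: the eligibility condition, the unadjusted comparison and the list of endpoints.

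**Stronger readings that do not hold.**
- A reader might infer from the broad pre-test sentence that untreated patients are recorded in phase 1 only. The enrolment sentence, the paired phase definitions and the Abstract contradict this.
- A reader might infer that bleeding rates would look better through dilution by non-stroke patients, and also that such patients vanish from the trial. These need opposite readings of eligibility and cannot both apply. The article gives no bleeding rates to size the first.
- A reader might say that only speed is measured. Bleeding and safety-climate items are measured too; what is absent from the list is the treated fraction and diagnostic accuracy.
- A reader might take 1.6 or 3.1 min as the expected bias. They are upper bounds under assumed shifts, with a spread borrowed from a heterogeneous regional network.

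**Conclusion.** The concern holds as a limit on interpretation. The primary analysis conditions on a decision taken after the intervention, and the unadjusted pre/post rank test cannot attribute a shorter median to process speed rather than case mix. The selection bias acknowledged in the Discussion is the one through consent, which is a separate matter.

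Direction and size are unknown. Under the log-normal assumption with log SD about 0.41, a 10% loss of the slowest cases lowers a 31-min median by at most about 1.6 min. Against the pilot difference that is 1.6/12, or about 13%; it would be a larger share of any smaller gain available to centers that start at 30 min or below. A milder change of case mix moves the median by about 1.3 min and raises rejection from about 5% to about 15% at 200 per phase. None of this shows that the trial's result would be wrong, and no change to the sample size follows. It supports a low-cost improvement in reporting, together with a correction of the inconsistent recording sentence.

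**What to change.** 1. Reword the pre-test recording sentence in Interventional Methods so that it agrees with the post-test sentence and with the phase definitions in Selection of Centers and Subjects.
2. State that the monitored screening log counts all direct-to-center admissions with suspected stroke, by center, in both phases.
3. State that every patient given alteplase for suspected stroke is included whatever the final diagnosis.
4. Report by phase, beside the primary result, the IVT rate among those admissions and the proportion of treated patients without a final stroke diagnosis.
5. Add two sensitivity analyses of the primary comparison: one restricted to confirmed strokes, and one adjusted for the baseline variables that the Design section says are already on the CRF. The adjusted one covers measured case mix only.

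Use the treated fraction as supporting information, not as a condition that decides how the result is read. A similar fraction does not prove a similar case mix, and the fraction may change for reasons that leave a real gain intact.

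The cost is a small documentation burden for the log count, one discharge-diagnosis field if the CRF does not already hold it, and two further analyses. Recruitment targets and trial procedures are unchanged.
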